## Methods

### Study Design

The study is a laboratory-based, (double-)blind, randomized controlled trial with three parallel arms: frequency-modulated researcher-selected music, unmodulated researcher-selected music and unmodulated self-selected music. Double blinding with respect to frequency modulation will be achieved in the researcher-selected music conditions, and participant blinding will be ensured regarding frequency modulation within the self-selected music condition. Figure 1 displays the study flow chart.

**Figure 1 F1:**
[figure not shown]
Study flow diagram.

Overall, 90 participants (30 participants per intervention condition) will attend a baseline assessment, followed by 10 sessions of music listening conducted within 3 consecutive weeks. Finally, post and follow-up assessments will be conducted. We do not anticipate protocol modifications. Nevertheless, if any trial modifications should be considered necessary, all changes in design, measures, or eligibility criteria will be recorded in the online protocol registration entry and will be included in the final manuscript for journal submission.

Following the study preparation phase (April–November 2016), recruitment and testing started in December 2016 in Marburg, Germany. Due to the move of our lab from Marburg, Germany, to Vienna, Austria, recruitment and testing needed to be paused as of January 2018 for 9 months. Testing continued in October 2018 and is presumed to be accomplished in December 2022.

### Study Setting and Procedure

All 13 appointments (baseline, 10 music-listening sessions, post-intervention assessment, follow-up assessment) will be held in our laboratory. Since previous research indicates that chronobiological rhythms influence perceived pain and stress parameters (96, 97), the appointments will be scheduled exclusively between 12 and 6 p.m. The 10 music-listening sessions (intervention period) will be scheduled within 3 consecutive weeks. Baseline and post-assessments will be held as closely in time as possible to the first and last music-listening session, respectively. Some degree of variability between participants will be accepted in order to better enable participants to fit the large number of appointments into their daily schedules.

After a telephone-based screening and upon inclusion, participants will be scheduled a baseline appointment and receive an email with instructions that they are asked to comply with in order to prevent any interference with behavioral and physiological measures (see Box 1).

Box 1Instructions for study appointmentsNo intake of analgesic medication on days of study appointmentsNo use of body lotion or other fatty agents in the chest area (before the appointment) to minimize artifacts in ECG recordings on days of study appointmentsNo consumption of alcoholic and/or energizing beverages or food, no smoking, no excessive exercise or relaxation techniques (i.e., meditation, yoga) for at least 1 hour prior to study appointmentsWearing of comfortable clothing during appointments.

Participants allocated to the self-selected music condition will also receive an email attachment instructing them to compile 120 min of their favorite music pieces. This self-selected music compilation should be brought to the first baseline assessment on a portable device and handed to the examiner. At the end of the baseline appointment, the examiner and participant arrange further appointments for the subsequent 10 sessions of music listening within the next 3 consecutive weeks.

At the beginning of each appointment, participants will be asked to indicate whether any of the behaviors mentioned in Box 1 (drinking alcoholic or energizing beverages, smoking, etc.) apply. Additionally, the examiner will document whether participants state being in a currently stressful phase (i.e., exams), had poor sleep quality or short sleep duration during the previous night, or have any current illness. Affirmation of intake of analgesic medication at baseline, music-listening sessions 1, 3, 6, 10, post-, or follow-up assessments will lead to rescheduling of the respective session since acute pain will be induced at these appointments. The detailed protocol and timeline for baseline, post, and follow-up appointments is displayed in Figure 2A, the protocol and timeline for music-listening sessions 1, 3, 6, and 10 is depicted in Figure 2B. The examiner will be blind regarding frequency modulation and will be in charge of instructing the participants during the course of the study. An independent second scientific staff member, unblinded with regard to intervention conditions, will be in charge of adjusting the music delivery systems (described below) according to the respective music-listening intervention. This person will not interact with the participants face-to-face at any time.

**Figure 2 F2:**
[figure not shown]
Protocol and timeline for study appointments: **(A)** baseline, post, and follow-up, **(B)** music-listening sessions 1, 3, 6, and 10.

### Study Population

Eligibility criteria are age between 18 and 35 years, body mass index between 18.5 and 30 kg/m^2^, fluency in speaking and reading German, and ability to attend our laboratory for 10 appointments within 3 consecutive weeks. Participants of both genders will be included (15 women and 15 men per group).

The following exclusion criteria are specified to ensure an accurate delivery of the music-listening interventions:

- Perfect pitch- Music-related studies (i.e., university level education) or profession- Impairment of hearing capability (e.g., chronic/acute tinnitus, hearing loss).

Additionally, since our primary and secondary outcome measures are susceptible to a range of lifestyle factors and health conditions (98, 99), and in order to reduce any potential risk related to participation in the study, the following further exclusion criteria will be applied based on participant self-report:

- Cardiovascular disease- Artery occlusive disease- Hyper-/Hypotension- Diabetes- Extreme visual impairment- Chronic pain condition- Raynaud syndrome- Irregular menstrual cycle- Pregnancy or breastfeeding- Inability to refrain from smoking for more than 2.5 h- Regular and problematic alcohol consumption- Regular intake of pain medication and/or psychotropic drugs- Mental disorders: current major depression/anxiety disorder; current eating disorder or eating disorder within the past 5 years, current substance abuse or substance abuse within the past 2 years; current or previous psychosis, schizophrenia, or bipolar disorder- Premenstrual syndrome- Inability to self-identify as a man or woman.

### Recruitment, Screening, and Consent

Participant recruitment will be conducted by advertising on public notice boards, internet classified ads, social media sites and via announcements in university classes. The study will be presented to the public as “Music for stress management: A music-based intervention study,” and a study email address will be given for contact purposes. Interested potential participants will be asked to send an email including their telephone number in order to establish a first contact.

A two-step screening approach will ensure that only healthy participants are included. First, prospective participants will complete a telephone-based screening interview to check for inclusion and exclusion criteria with regard to medical conditions and lifestyle factors. Thereafter, the detailed study information and an online link to confirm or decline study participation will be sent to the positively screened participants. In the case of confirmation, participants will be emailed a subsequent link leading to an online survey including a battery of questionnaires with further in-depth inclusion and exclusion criteria. If participants screen positive for depression, pre-menstrual syndrome or any psychiatric disorders apply [either based on self-report within the telephone screening or based on the online questionnaires, e.g., Patient Health Questionnaire (100), Beck Depression Inventory-II (101), Premenstrual Syndrome Questionnaire (102)], they will be excluded from the study. If no exclusion criteria apply, participants will be randomly allocated to one of the three music-listening interventions, and the baseline appointment will be scheduled. The informed consent obtained online will be corroborated by a personal signature at baseline. Participants will be compensated for completion of the study with 80 €. In the case of pre-mature termination of the study, participants will be compensated proportionally.

### Randomization

We will use a block randomization stratified by gender using the blockrand package (103) and the statistical software R, version 3.4.2 (104). Block lengths will vary randomly between 3, 6, and 9. The randomization procedure will be performed by an independent researcher unrelated to the study. The resulting 90 computer-generated notes stating participant gender and experimental condition will be placed into separately sealed envelopes and stored in a locked cabinet. Upon inclusion of a new participant, the project coordinator will draw an envelope containing the note with the respective condition to which the included participant will be assigned. This information will be shared with the scientific co-worker who will be in charge of setting the music-delivery systems (see below) during the course of the intervention period, but not with the experimenter.

### Blinding

To ensure that all participants across all conditions have similar beliefs in terms of treatment expectancy, participation in the study (as stated in the study information) implies random assignment to either frequency-modulated or unmodulated music, irrespective of selection of music (researcher- vs. self-selection). The modulation of frequencies in our intervention is not or only barely audible as confirmed in a pilot study conducted in our own lab. Therefore, participants will be unable to detect whether the music they listen to is frequency-modulated (or not), and we will check participants' assumptions concerning their assigned condition at the end of the study (as described below).

With regard to frequency modulation in the researcher-selected conditions, the participants and the examiner (who will be in charge of instructing and interacting with the participants throughout the study sessions) will be fully blinded. Similar to participants in the researcher-selected music conditions, participants in the self-selected music condition will expect to hear either frequency-modulated or unmodulated music. Due to technical constraints, however, frequency modulation will not be applied in this study arm and participants will be exclusively listening to unmodulated music. In this case, the examiner interacting with the participants will be aware of the fact that no frequency modulation will be applied. Consequently, apart from the examiner's and participants' awareness of researcher-selected vs. self-selected music, the study features a double-blind design (examiner and participant) with regard to the frequency modulation within the researcher-selected music arms and a single-blind design (participant only) with regard to the self-selected music arm. The scientific co-worker who will be in charge of the music-delivery systems and administering the correct music intervention to the participating subjects will be fully aware of the respective conditions. Moreover, the study coordinators will also be unblinded since they will be in charge of assigning participants to examiners and scientific co-workers. Neither scientific co-workers nor study coordinators will interact directly with the participants.

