##### Primary Outcomes

Pain tolerance and perceived pain intensity: Pain tolerance will be operationalized via time in seconds elapsed from immersion until extraction of the hand during the CPT. It will be recorded by the examiner using a stopwatch. Perceived pain intensity will be measured before and after the CPT via paper-and-pencil visual analog scales (VAS). Participants will be provided with a piece of paper containing the sentence “I am in pain” and a 10 cm line ranging from 0 to 100. They will be instructed to mark the line accordingly (0 = no pain, 100 = maximal pain). Additionally, after the CPT, participants will be asked to report how painful they perceived the CPT to be by responding to the sentence “The test was painful” and again marking a VAS corresponding to their experience (0 = not at all painful, 100 = maximally painful). Measures of pain perception will be assessed at baseline, post, and follow-up as well as after music listening in sessions 1, 3, 6 and 10 (see Table 1 and Figure 2).

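### Staff who know the allocation assign each participant's examiner, so the person who instructs the cold pressor test and times pain tolerance can differ by arm

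*Protocol article*

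**What the plan says.** Under Recruitment, Screening, and Consent, once no exclusion criteria apply, "participants will be randomly allocated to one of the three music-listening interventions, and the baseline appointment will be scheduled". Every cold pressor test, including the one at baseline, therefore follows allocation.

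Under Randomization, "the project coordinator will draw an envelope containing the note with the respective condition to which the included participant will be assigned". The condition is then passed to the co-worker who sets the music system and withheld from the experimenter. The list is stratified by gender only ("We will use a block randomization stratified by gender using the blockrand package").

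Under Blinding, "the study coordinators will also be unblinded since they will be in charge of assigning participants to examiners and scientific co-workers". The examiner is described there as the person "who will be in charge of instructing and interacting with the participants throughout the study sessions". The same section says that coordinators and music co-workers have no direct contact with participants. Examiners are blind to modulation in the two researcher-selected arms, but in the self-selected arm "the examiner interacting with the participants will be aware of the fact that no frequency modulation will be applied".

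Under Primary Outcomes, pain tolerance is the time from immersion to extraction of the hand: "It will be recorded by the examiner using a stopwatch". Pain intensity is marked by the participant on a paper visual analog scale. Under Pain Induction, participant and examiner face away from each other, the participant signals withdrawal verbally, and immersion ends at 3 minutes.

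**The concern.** Pain tolerance in a cold pressor test depends on effort, and so on how the test is introduced and run. Examiners can differ in this. Randomisation balances what participants bring with them. It does not balance an operator chosen afterwards by someone who knows the result of the draw. If one examiner sees a larger share of one arm, that examiner's effect can be read as an effect of the music.

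This needs no intent. In the self-selected arm the examiner also receives the participant's compilation and transfers it to the server and the delivery system. A scheduler who knows the arm could reasonably give those participants to particular staff.

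The timing part of the concern applies to pain tolerance. The instruction part applies to both primary outcomes.

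**Working it through.** The article states no figure on this point, so there is nothing to reproduce. The check is a reading of the sections together, followed by algebra for the planned contrast and an illustration of scale.

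**1. Do the stated safeguards cover examiner choice?**
- Examiner blinding to modulation limits expectation between the two researcher-selected arms. It does not control which examiner is sent to which arm.
- Lack of contact between coordinators and participants closes a different route.
- Facing away during the test limits social cues. Instruction and timing stay with the examiner.
- Stratification covers gender, not examiner.

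None of these makes examiner mix independent of arm.

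**2. What reaches the planned contrast?** Main hypotheses 1 and 2 concern change from baseline to post, and Sample Size Determination describes a condition-by-time design. Take two examiners whose effects on the score differ by D. Let the first examiner's caseload share be p1 in one arm and p2 in the other.
- Comparison at one time point: bias = (p1 − p2) × D.
- Change score in general: bias = (p1 − p2 at post) × D at post − (p1 − p2 at baseline) × D at baseline.
- Same examiner kept, constant D: bias = (p1 − p2) × (D − D) = 0.
- Same examiner kept, D varying over time: bias = (p1 − p2) × (D at post − D at baseline).
- Examiners switch, constant D: bias = D × [(p1 − p2 at post) − (p1 − p2 at baseline)]. This is zero when switching is unrelated to arm. Such switching adds noise, not bias.
- The 3-minute cap (180 s) makes D vary. As more participants reach the cap, the examiner difference shrinks there, so D at post need not equal D at baseline.

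**3. Scale, on assumed inputs.** From the article: 30 per arm, two-sided alpha 0.05. Assumed: D from 0.25 to 0.8 SD and the caseload splits below.

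Standard error of an arm difference at one time point = sqrt(2/30) = 0.258 SD.
- 0.5 × 0.20 = 0.10 SD, and 0.10/0.258 = 0.4 standard errors.
- 0.5 × 0.40 = 0.20 SD, and 0.20/0.258 = 0.8 standard errors.

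Bias in SD, with simulated two-sided type I error in brackets (t-test, 30 per arm, 40,000 runs per cell):

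| D | 50/50 in both arms | 60/40 v 40/60 | 70/30 v 30/70 | 80/20 v 20/80 |
|---|---|---|---|---|
| 0.25 SD | 0 (0.049) | 0.05 (0.053) | 0.10 (0.066) | 0.15 (0.087) |
| 0.5 SD | 0 (0.050) | 0.10 (0.065) | 0.20 (0.115) | 0.30 (0.200) |
| 0.8 SD | 0 (0.048) | 0.16 (0.089) | 0.32 (0.213) | 0.48 (0.417) |

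Here D is the examiner difference in whatever score is analysed. For the change score with one constant examiner per participant, D is 0 and the table does not apply.

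**The case against.** The strongest reply is that the planned analysis largely protects itself. Allocation precedes baseline, participants (not sessions) are assigned to examiners, and the Blinding and Study Setting and Procedure sections describe one examiner acting throughout. Continuity is the natural reading, and a constant examiner effect then drops out of the time-by-condition test. This stands. A reader might infer that an examiner effect passes straight into the main arm comparison. The documents do not support that. They do not guarantee continuity either, and the effect need not be constant.

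The article also does not say outright that the examiner is chosen after the envelope is opened, or that the project coordinator who draws it is one of the study coordinators who assign staff. A full protocol may hold a rota. This stands as far as it goes. But the article itself gives assignment to examiners as a reason why the coordinators are unblinded, so the point rests on a stated procedure, not on silence.

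A reader might further infer that only the music co-worker needs to know the arm. That is wrong. Self-selected participants must be sent playlist instructions before baseline, and the examiner handles their music. What examiner assignment does not need is modulated versus unmodulated status within the researcher-selected arms, and the article gives no reason why it would.

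Finally, nothing shows that uneven assignment has occurred. Playlist handling gives no route to imbalance between the two researcher-selected arms. Both points are correct: the plan leaves the route open, and no more than that can be said.

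**Conclusion.** The point holds in a limited form. Staff who know the allocation assign the examiner who instructs the participant and times a primary outcome, and no stated safeguard keeps examiner mix independent of arm. The exposure is to:
- comparisons at a single time point;
- change scores when examiners switch in an arm-related way;
- change scores when the examiner effect varies over time or interacts with the 3-minute cap.

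If one examiner is kept and the effect is constant, the baseline-to-post contrast is unbiased.

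The size cannot be derived from the article, which gives no number of examiners, no examiner differences and no caseloads. The illustrative 0.10 to 0.20 SD rests wholly on an assumed 0.5 SD examiner difference and a 20- to 40-point difference in share, and it describes a single-time-point comparison. It should not be quoted as an expected bias in the main test. The change is worth making because the route is avoidable at very little cost.

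**What to change.** For participants still to be included:
- Assign the examiner from a fixed rota and record the assignment before the envelope is drawn.
- Keep that examiner for baseline, post and follow-up where scheduling allows.
- After opening, limit knowledge of modulated versus unmodulated status to the coordinator who opens the envelope and the music co-worker. Self-selected status must still be known to the staff who send the playlist instructions and to the examiner.
- Record the examiner code at each cold pressor test.

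In the report, give the distribution of examiners by arm at each assessment. If it is uneven, add a sensitivity analysis adjusted for examiner. For participants already tested, the table can be compiled if the session records identify the examiner.

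The cost is a reordered administrative step, one extra field on the session form and a mild scheduling constraint. The constraint comes from keeping one examiner across visits when all appointments fall between 12 and 6 p.m. No extra participants are needed.

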### Debriefing

At the end of the post-assessment, participants will be asked to indicate which condition they believe they were allocated to (i.e., frequency-modulated or unmodulated music) in order to check if blinding has been successful. After termination of the study (i.e., after the completion of the follow-up assessment), participants will be debriefed with regard to their intervention allocation. They will be further debriefed with regard to the study goals and the fact that no frequency modulation occurred in the self-selected music-listening condition. In the case of premature study termination, participants will be debriefed accordingly.

### Music-Listening Interventions

Each of the three music-listening interventions consists of 10 sessions of music listening within 3 consecutive weeks. There is no pre-defined minimum number of sessions per week in order to ensure integration of the intervention into participants' schedules. We chose a highly concentrated number of intervention sessions since we assume a dose-dependent effect on measures of pain perception and markers of stress (38, 105). Each music-listening session will encompass 60 min of music listening and 10–20 min for additional data assessments before and after music listening. Participants will receive the intervention individually. During music listening, each participant will be in a reclined position on a lounge chair and will listen to the allocated music via headphones.

#### Frequency-Modulated Researcher-Selected Music

Frequency modulation and music pieces used in this arm are comparable to the procedures of applications of AVWF-based music interventions in previous clinical studies (74, 75). Six different mixes of music pieces are chosen that cover a wide range of genres such as classic, instrumental, pop, rock, and world music (see Box 2 for details). Three of these mixes are compositions of known artists of which two also contain vocals. The remaining three of the music mixes are instrumental music pieces that were directly composed, recorded, and provided by the developer of the AVWF method. Four of the six mixes will be presented repeatedly within the 10 music-listening sessions. Each mix has a length of 60 min. According to the AVWF method, the applied music is modulated within the audible frequency range of 50–4,000 Hz via a software system. This involves filtering the harmonic overtones of low frequencies of the music pieces presented in music-listening sessions 1–7. In sessions 8–10, modulation will be additionally applied to frequencies in the high spectrum. The modulated music will be transferred onto a music delivery system (described below) which is equipped with hardware components and additional modulating features, increasing the magnitude of modulation from session to session. This treatment is based on the assumption that listening to music modulated in the low- and high-frequency spectrum improves stress regulation and benefits the ANS via indirect stimulation of afferent and efferent nerves within the auditory passage (106).

Box 2Overview of the music used in each music-listening session in the researcher-selected music conditions.

